#### Child Motivation

##### Overview

Intrinsic motivation, an internal drive to seek out new and challenging experiences to learn and expand one’s abilities [40], has been associated with performances on cognitive training activities and outcomes in children [41-43] and adults [44]. We measured aspects of children’s motivation to rule out the potential influence of differences in expectations between the working memory training conditions and the active control [1,45].

##### Motivation Toward Classroom Activities

Children’s motivation toward typical classroom activities was measured using the Intrinsic Motivation Scale (IMS) [46]. The IMS consists of 3 subscales: challenge (6 items; eg, I like hard work because it’s difficult), curiosity (6 items; eg, I ask questions in class because I want to learn new things), and independent mastery (5 items; eg, I like to try to figure things out at school on my own). The child responded using a 3-point Likert scale (yes: 3 points; sometimes: 2 points; no: 1 point). The IMS has very high internal consistency (0.90) and high test-retest reliability with a 6-week interval (0.74) [46].

##### Motivation Toward the Intervention

Children’s motivations toward the intervention were measured using a modified Intrinsic Motivation Inventory (IMI) [47], which has been used in child cognitive training studies [41-43]. This modified IMI consists of 4 subscales: interest or enjoyment (7 items; eg, it was fun to do), perceived competence (6 items; eg, I think I am pretty good at the training), effort or importance (5 items; eg, I put a lot of effort into it), and value or usefulness (4 items; eg, I think the training could help me). Identical to the IMS, the child responded on a 3-point Likert scale. This modified IMI has been used in a previous randomized control trial of working memory training with similar-aged children and has high internal consistency (≥0.74) [41].

### Data Management and Confidentiality

Personal and trial data were collected and managed using REDCap electronic data capture tools hosted and managed by Helix (Monash University) [48,49]. Personal data required to disseminate the caregiver questionnaires were held securely and will not be used for any other purpose. Given the sample size, the trial’s timeframe, and the minimal risks associated with participation, there is no data monitoring committee.

### Procedures

Children participated in testing sessions, and caregivers completed behavioral questionnaires at baseline, immediately, and 6 months postintervention. The baseline and immediately postintervention measures were completed 1 week before and after the intervention, respectively. The 6-month postintervention measures were completed approximately 26 weeks postintervention (±8 weeks due to school term breaks).

Children were tested in small groups of 6 to 8. The group child testing sessions were led by a doctoral provisional psychologist and conducted in a quiet room on the primary school campus. The test order and administration protocol was the same at each time point. Children first completed the working memory measures on an iPad with headphones to reduce distraction, the Raven’s SPM, and then motivation questionnaires. General task instructions were delivered to the children as a group. Children were encouraged to ask clarifying questions, and the researcher responded with standardized additional instructions and ensured the child understood how to complete the task before proceeding with testing.

### Power Calculations and Sample Size

Calculations in G*Power (effect size *f*^2^=0.07; 80% power; α=.05) [50,51] indicated a sample size of 29 children per condition would be required to detect a small to moderate effect of each working memory training condition (adaptive, self-select, and stepwise) compared to the active control on the near transfer measures immediately postintervention (primary outcome). This effect size was based on previous research, which indicates working memory training programs produce a small to moderate effect compared to a control condition on near transfer measures [6,17]. The target sample size was increased to 32 children per condition to account for 10% attrition [22]. Our previous school-based trial of a working memory training program had a 65% child recruitment rate [22]. Thus, to achieve our target sample size, the participating primary school had to have at least 197 children enrolled in grades 2 to 5.

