**Conclusions:**

This trial will determine whether the adaptive approach to setting the difficulty of training activities maximizes cognitive training outcomes for children. This trial has several strengths: it adopts best practices for cognitive training studies (design, methods, and analysis plan); uses a range of measures to detect discrete levels of transfer; has a 6-month postintervention assessment; is appropriately powered; and uses an experimental working memory training intervention based on our current understanding of the cognitive mechanisms of training. Findings will inform future research and design of cognitive training interventions and highlight the value of the evidence-based principles of cognitive training.

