Working memory training provides the ideal testbed to systematically examine the assumption that the adaptive approach maximizes cognitive training outcomes. It is one of the most widely studied domains in the cognitive training literature [17,18]. Working memory is a mental workspace capable of holding and processing information for brief periods in the course of ongoing cognitive activity [19]. This ability is critical for children’s learning as it facilitates a host of complex cognitive activities such as comprehension, reasoning, and problem-solving [20]. Indeed, low working memory is commonly associated with poor scholastic attainments [20,21]. Meta-analyses examining near transfer effects following cognitive training reveal the highest effect sizes for training targeting working memory (*g*=0.50) than either inhibitory control (*g*=0.24) or cognitive flexibility (*g*=0.37) [6,17]. Evidence from high-quality trials also demonstrates near transfer effects of working memory training programs in children, such as Cogmed [15,22] and Braintwister [16,23]. However, there is less support for intermediate transfer, and the evidence for far transfer is negligible when methodological issues, such as the lack of an active control group, are taken into account [6,8,17,22,24-26].

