### Statistical Analysis

Primary analyses will be intention to treat (ITT) with sensitivity analyses only with children who completed the allocated intervention. Primary analyses will be separate linear regressions for each primary outcome at the primary end point (immediately postintervention) as the dependent variable, the outcome at baseline and the stratification factor (age) as covariates, and conditions (dummy coded with the active control as the reference) as the independent variables. Statistical significance will be set at α=.05 (2-tailed). If outcomes do not meet the normality assumption, a nonparametric bootstrap will be used. Effect sizes and 95% CI will be reported to demonstrate the magnitude of differences in outcomes between each training condition relative to the active control. Bayesian methods will be used to quantify the strength of evidence in favor of the null hypothesis and the alternative hypothesis. Interpretation of results will consider the strength of effects and *P* values. The same analytic approach will be applied to secondary outcomes and to both primary and secondary outcomes at the 6-month postintervention time point.

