This trial has important strengths. The trial design, methods, and analysis plan are in line with best-practice standards for cognitive training trials [1]. The trial was randomized, participants and assessors were blinded, and an active control condition was used. The active control condition (instead of a passive or no-contact control) was designed to be believable as an intervention, indistinguishable from the working memory training conditions in terms of the environment and motivating features, and thus was designed to ensure children experience a similar level of engagement, and experimenter and teacher attention to children allocated to the working memory training conditions. The set of outcome measures was designed to detect discrete levels of near transfer by minimizing confounders associated with training effects [4], and intermediate and far transfer effects are measured too. Training outcomes were assessed immediately postintervention and again at 6-month postintervention to determine any persisting training benefits. The trial is sufficiently powered to detect differences between the working memory training conditions and the active control condition. Importantly, our novel experimental working memory training interventions are designed specifically for this research and reflect the current understanding of the cognitive mechanisms of training: the processing demands of the training activities are (1) sufficiently unfamiliar such that the child needs to generate novel cognitive routines to do well, and the routines can then be applied to new activities that are similar but untrained; and (2) overlap with daily activities, such as following teacher directions, which overlap with daily activities. This is the first time the following instructions paradigm has been used as a working memory training activity. The nonadaptive approaches used in this trial reflect a similar approach to learning that children experience in daily activities, such as having autonomy over their learning (self-select), and mastering simpler concepts before complex concepts (stepwise). Motivation questionnaires will be used in analyses to determine if children in the training and active control conditions have similar motivation toward learning in the classroom and expectations of the intervention.

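### The 29 per condition comes from a four-arm total; per contrast it gives 80% power for about 0.74 residual SD, so 80% power at the cited g=0.50 is not supported without a strong covariate assumption

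*Protocol article*

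**What the plan says.** Power Calculations and Sample Size gives the inputs as "Calculations in G*Power (effect size *f*^2^=0.07; 80% power; α=.05" and concludes that "a sample size of 29 children per condition would be required to detect a small to moderate effect". The effect meant is that of every training arm taken singly against the active control, for near transfer straight after the intervention. The section justifies the effect size by two references on training versus control. The Background cites the same two references for meta-analytic near-transfer effects, with the highest value for "training targeting working memory (*g*=0.50".

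Statistical Analysis plans one linear regression per primary outcome, with condition indicators referenced to the active control and with baseline score and age as covariates. It adds: "Statistical significance will be set at α=.05 (2-tailed".

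Two further places claim adequate power without qualification. The Abstract's Conclusions say the trial "is appropriately powered", and the Discussion says: "The trial is sufficiently powered to detect differences between the working memory training conditions and the active control condition".

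**The concern.** Cohen's f² for one regression coefficient depends on how the sample is divided. In a two-group study every child informs the single contrast. In a four-arm study with a shared control, about half the children inform any one training-versus-control contrast, beyond helping to estimate the residual variance and covariate slopes. The same f² therefore stands for a larger difference between two arms in the four-arm design.

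The article ties f²=0.07 to a small to moderate effect of training against control, which is a two-group quantity. If 0.07 corresponds to a much larger difference per contrast, the claim of 80% power for each arm does not hold at the effect cited. At stake is how readers weigh a non-significant arm: a trial described as adequately powered lends such a result more weight than the design may justify.

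**Working it through.** **Inputs.** From Power Calculations and Sample Size: f²=0.07, 80% power, α=.05, 29 per condition (4 × 29 = 116), each training arm against active control. From Statistical Analysis: two-tailed test; three condition indicators plus baseline and age as covariates. From the Background: g=0.50. Not given in the article, so assumed over a range: R², the share of within-arm outcome variance explained by baseline score and age together. I take g to be in within-arm outcome SD.

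**1. Reproducing the 29.** For one coefficient (1 numerator df), noncentrality is λ = N × f². With f²=0.07 and a two-sided 5% test, the smallest N with 80% power is 115, for any number of predictors from 1 to 6. Then 115/4 = 28.75, rounded up to 29; at N=116 power is 80.6%. Other readings do not give 29:
- a one-sided test needs N=90 (22.5 per arm);
- α=0.05/3 needs N=153 (38.25 per arm);
- f²=0.07 applied to the 58 children of one contrast gives only 51% power.

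So the 29 is a four-arm total divided by four.

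**2. What f²=0.07 means for one contrast.** With n per arm and a difference of d residual SD, λ = d² × n/2. With four equal arms n = N/4, so λ = N × d²/8 and f² = d²/8. Hence d = √(8 × 0.07) = √0.56 = 0.748. With two arms making up the whole sample, n = N/2, f² = d²/4 and d = √(4 × 0.07) = 0.529.

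Solving directly with the noncentral t distribution (29 per arm, about 110 df), the difference detectable with 80% power is 0.742 residual SD. A 10,000-run simulation of the planned regression gave 79.6% power at 0.748 and 46.8% at 0.50 residual SD.

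**3. Power at the cited effect.** In the four-arm model, 0.50 residual SD is f² = 0.25/8 = 0.031, under half of 0.07. Covariates shrink the residual SD, so the effect in residual SD is 0.50/√(1−R²), and the detectable difference in outcome SD is 0.742 × √(1−R²).

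| Assumed R² (correlation) | Detectable at 80%, outcome SD | Power at g=0.50, 29 per arm |
|---|---|---|
| 0 (0) | 0.74 | 47% |
| 0.25 (0.5) | 0.64 | 59% |
| 0.49 (0.7) | 0.53 | 75% |
| 0.56 (0.75) | 0.49 | 81% |
| 0.64 (0.8) | 0.45 | 88% |

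**4. Where 80% is reached.** R² = 1 − (0.50/0.742)² = 0.55, a correlation of √0.546 = 0.74.

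**5. If all 32 per arm were retained.** The detectable difference is 0.706 residual SD, power at 0.50 residual SD is 51%, and 80% at g=0.50 needs R² = 1 − (0.50/0.706)² = 0.50. The conclusion is the same.

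**The case against.** The strongest reply is that nothing in the calculation is arithmetically wrong. The article states 80% power at f²=0.07, and that reproduces for one coefficient of the planned regression. This stands. A reader might infer that the 80% figure itself is an error; the documents do not support that. What lacks support is equating this f² with the training-versus-control effect that the article cites.

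Second, a reader might infer that the authors converted g=0.50 to f² by the two-group rule. That is plausible, because 0.07 corresponds to d=0.53 on that rule, but the article shows no conversion. Converting 0.50 exactly gives 0.50²/4 = 0.0625, which leads to a total of about 128, or 32 per arm before attrition, not 29. The origin of 0.07 is therefore an inference, and the point does not depend on it.

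Third, the shortfall is conditional. The primary outcomes are span tests in children aged 7 to 11, and baseline and age may together explain much of the variance. At R² of 0.56 or 0.64 power exceeds 80%. This stands too: the documents do not show that the trial is underpowered, nor do they set any upper limit on its power at g=0.50. The assumed R² may be in a fuller document not shown. Yet the article states inputs, result and claim together without invoking covariate gain, and as written they do not match.

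Fourth, a reader might infer that non-significant arms will be taken as proof of no effect. Statistical Analysis plans effect sizes with 95% confidence intervals, Bayesian evidence for null and alternative, and interpretation by strength of effect as well as P value. This limits the harm considerably but leaves the power claim uncorrected. The Discussion's admission that comparisons between training arms are not powered does not cover the contrasts with control.

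**Conclusion.** The point holds in a limited form. With 29 analysed per arm, each training-versus-control contrast has 80% power for 0.74 residual SD. The article does not support 80% power at g=0.50 unless baseline score and age explain about 55% of outcome variance, which it neither states nor invokes. Over assumed R² from 0 to 0.64, power at g=0.50 runs from 47% to 88%. A smaller effect within a small-to-moderate range would have lower power at each R².

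This rests on equal arms, a common residual variance, g in within-arm outcome SD, and the planned two-sided 5% test of each contrast. It should be fixed, as a correction to a stated property of the design. It does not invalidate the planned analysis.

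**What to change.** Replace the power statement in Power Calculations and Sample Size with one on the scale of the planned contrasts, for example:

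> With 29 analysed children per arm, each training-versus-control contrast has 80% power for a difference of 0.74 residual SD. This equals 0.64, 0.53 or 0.49 outcome SD if baseline score and age together explain 25%, 49% or 56% of outcome variance. Power at g=0.50 is 47%, 59%, 75%, 81% and 88% at R² of 0, 0.25, 0.49, 0.56 and 0.64. These R² values are assumptions.

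If an R² or correlation was assumed at planning, state it, and state how f²=0.07 was obtained. Qualify the power claims in the Abstract's Conclusions and in the Discussion to match. In the results paper, interpret non-significant arms from the confidence intervals and Bayesian evidence already planned.

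The cost is wording and a less favourable power figure. Data collection ended in December 2022, and neither enrolment nor the analysis model changes.

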### Statistical Analysis

Primary analyses will be intention to treat (ITT) with sensitivity analyses only with children who completed the allocated intervention. Primary analyses will be separate linear regressions for each primary outcome at the primary end point (immediately postintervention) as the dependent variable, the outcome at baseline and the stratification factor (age) as covariates, and conditions (dummy coded with the active control as the reference) as the independent variables. Statistical significance will be set at α=.05 (2-tailed). If outcomes do not meet the normality assumption, a nonparametric bootstrap will be used. Effect sizes and 95% CI will be reported to demonstrate the magnitude of differences in outcomes between each training condition relative to the active control. Bayesian methods will be used to quantify the strength of evidence in favor of the null hypothesis and the alternative hypothesis. Interpretation of results will consider the strength of effects and *P* values. The same analytic approach will be applied to secondary outcomes and to both primary and secondary outcomes at the 6-month postintervention time point.

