### Randomization

Following baseline testing, children were randomized to 1 of the 4 number-coded conditions (adaptive, self-select, stepwise working memory training, or active control) using a randomization scheme generated in advance and set up in Research Electronic Data Capture (REDCap) hosted at Monash University by the trial statistician ([name]) who was not involved in data collection. Specifically, block sizes of variable size (4 or 8) were used to assure allocation concealment and preguessing of the allocation sequence at the end of each block. Randomization was stratified by age at baseline: 7 to 8 years, 9 to 10 years, and 11 years.

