**Figure 2 figure2:**
[figure not shown]
The working memory training activities: (A) backward span and (B) following instructions. ms = milliseconds, ISI = Interstimulus Interval.

In the backward span training activity, a series of digits were presented auditorily, and the child had to remember and immediately recall in reverse order the sequence of items by tapping the digits on the iPad screen. The difficulty level was manipulated by increasing the number of digits to be recalled. The following instructions training activity is based on a classroom analog test of working memory developed by Gathercole et al [29]. In this training activity, the child was introduced to 3 objects, each object comes in 3 colors, and 2 actions that require different tapping responses on the iPad screen. The child had to remember and immediately implement an action-color-object sequence (eg, break the red wire, then place the blue button, reflecting a span of 2) by using the relevant tapping response on the screen of the iPad with the corresponding color-objects. Difficulty level was manipulated by increasing the number of action-color-objects in the sequence the child has to perform. Each activity comprised 5 blocks of trials per session, and each block had 4 trials of a span level (per session: total 20 backward span trials, then 20 following instructions trials).

In this trial, there were three different working memory training conditions, each with a different approach to adjusting the difficulty level of the training activities: (1) *adaptive* condition, the difficulty level adapted to the child’s performance during each training session on a block-by-block basis for the first 4 blocks (adapted between block 1 to 2, block 2 to 3, and block 3 to 4, and block 5 retained the same difficulty as block 4) within the training sessions for each activity; (2) *self-select* condition, the child decided at the end of each session if they would like a training activity to be easier, the same, or more difficult in the next session; and (3) *stepwise* condition, the difficulty level increased incrementally across sessions and this progression was predetermined and stratified by age based on current understanding of the development of children’s working memory: 7 years, 8 to 9 years, and 10 to 11 years [30].

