**Near transfer**									
	Backward span digits	Child		✓		Primary outcome		✓	
	Following instructions objects	Child		✓		Primary outcome		✓	
	Backward span letters	Child		✓		✓		✓	
	Following instructions letters	Child		✓		✓		✓	

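### The primary regressions are valid but leave three baseline near-transfer scores unused; prespecifying them could add some precision at little cost

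*Protocol article*

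**What the plan says.** The Statistical Analysis section of the protocol article specifies "separate linear regressions for each primary outcome at the primary end point (immediately postintervention) as the dependent variable". The covariates are "the outcome at baseline and the stratification factor (age) as covariates", with three dummy variables comparing each training condition with active control. It adds "Statistical significance will be set at α=.05 (2-tailed").

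Table 1 lists four near-transfer tests, all given at baseline. Two are primary outcomes (backward span digits and following instructions objects). The other two, such as "Backward span letters", are secondary. Each primary model therefore uses one of the four baseline scores.

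The Power Calculations and Sample Size section gives "effect size *f*^2^=0.07; 80% power; α=.05" and concludes that "a sample size of 29 children per condition would be required". No standard deviation, baseline-to-post correlation or assumed R² is stated.

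**The concern.** The Near Transfer section says each test has four trials per span level and ends at the first level with fewer than three correct. A single score from such a test may carry appreciable measurement error, although the article reports neither the scoring nor the reliability. The other three tests share the paradigm or the domain, so their baseline scores may say more about the ability that drives the post-test.

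Precision matters because the sample is modest and the Results section says data collection has ended. The covariate set is one of the few things that can still narrow the intervals. If the extra scores are prognostic, the plan forgoes precision that the trial has already paid for.

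**Working it through.** **1. The plan's own figure.** I treated it as a two-sided test of one regression coefficient with f² = 0.07. The noncentrality is √(f²·N). N = 115 gives 80.3% power. With four equal arms, N = 116 (29 each), the noncentrality is √(0.07 × 116) = 2.850 and power is 80.6%. The stated 29 per condition reproduces without extra covariates.

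**2. What that effect means.** For one arm against control at 29 per arm, 2.850 / √(29/2) = 2.850 / 3.808 = 0.748 residual SD. The Background section cites g = 0.50 for near transfer of working memory training. If that g is in raw SD units, reaching 0.748 residual SD needs covariates explaining 1 − (0.50/0.748)² ≈ 0.55 of outcome variance.

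**3. Residual degrees of freedom.** Planned model: 116 − 1 − 3 (conditions) − 1 (baseline) − 2 (age bands) = 109. With three more scores: 106.

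**4. Formula for the gain.** Let r be the own-baseline-to-post correlation, c the correlation of each other baseline test with the post-test, b the intercorrelation of the baseline tests, and a the correlation of age with every test. All are assumptions. Age is already in the model, so remove it first: replace each ρ by ρ′ = (ρ − a²)/(1 − a²). Then:

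- planned R² = a² + (1 − a²)·r′²
- fractional cut in residual variance = [(c′ − b′r′)² / ((1 + 2b′)/3 − b′²)] / (1 − r′²)
- power: two-sided noncentral t, noncentrality 0.50/√(1 − R²) × √(29/2), on 109 or 106 df

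**5. Worked case, r = .6, c = b = .5, a = .4.**

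- r′ = .44/.84 = .524 and c′ = b′ = .34/.84 = .405.
- Cut = [(.405 − .405 × .524)² / (.603 − .164)] / (1 − .274) = (.0372/.439)/.726 = 11.7%.
- R² goes from .390 to .462, and power from 67.6% to 72.9%.
- Leaving age out gives a 15% cut for the same r, c and b, so ignoring age overstates the gain.

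**6. Range.** r = .5, .6, .7; c = .3, .4, .5; b = .4, .5, .6 with c ≤ b; a = .3, .4, .5. That makes 72 combinations.

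| r, c, b, a | variance cut | power, planned | power, four baselines |
|---|---|---|---|
| .5, .5, .5, .3 (largest gain) | 17.9% | 60.1% | 68.6% |
| .6, .5, .5, .4 | 11.7% | 67.6% | 72.9% |
| .7, .5, .5, .5 | 6.2% | 77.8% | 80.3% |
| .6, .4, .5, .4 | 1.7% | 67.6% | 68.3% |
| .5, .3, .5, .4 (no gain) | 0.0% | 61.5% | 61.5% |

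Across the 72 combinations the cut runs from 0 to 18% and the power gain from 0 to about 8 points. The median combination gives a 2.4% cut and a gain of about 1 point. Where the extra scores add nothing, the three lost degrees of freedom cost less than 0.1 point of power.

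**The case against.** The strongest reply is that nothing here is wrong. Adjusting for the same test's baseline and the stratification factor is valid, standard and prespecified, and the sample size reproduces without further covariates. All of this stands. The gain rests on correlations the article does not give, and it can be nil. Replacing a published primary model after data collection has ended also carries its own risk, and complete-case fitting with more covariates could lose children. Both risks bear on how the change is made, not on whether it can help.

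A reader might infer several stronger points that the documents do not support:

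- **That the plan certainly loses precision.** No correlation is reported, and a zero gain lies within the plausible range.
- **That the gain is much larger.** A 24% variance cut, with power rising to 77%, follows from r = .6, c = .5, b = .4 with age left out. That needs another test to predict the later score better than it correlates with the same test at the same sitting, which is unlikely.
- **That the trial is shown to be underpowered.** Step 2 indicates why precision is useful. But the article does not say how f² was derived or what R² lies behind it.
- **That the age bands conflict.** The Randomization section says "Randomization was stratified by age at baseline: 7 to 8 years, 9 to 10 years, and 11 years", while the stepwise progression uses "7 years, 8 to 9 years, and 10 to 11 years". The first governs allocation and the second sets training content in one arm. They need not match, no bias follows, and extra baseline scores would not change this.
- **That exact age is discarded.** The text does not settle whether age enters in bands or in years, and the bands already carry most of the age information.

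**Conclusion.** The point holds as an optional efficiency improvement. The planned regressions are sound, but they use one of four near-transfer scores taken at baseline. Under the stated assumptions, adding the other three lowers residual variance by about 0 to 18%, which is at most about a 9% smaller standard error (√(1 − 0.179) = 0.906). Power for a standardised difference of 0.50 at 29 per arm rises by about 0 to 8 points, with much of the range near the low end. The gain is larger when the own-test correlation is modest and the other tests predict the post-test about as well as they correlate with each other at baseline. The possible loss is three residual degrees of freedom of about 109.

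**What to change.** Before anyone sees outcomes by condition, prespecify in a dated document:

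- In every near-transfer regression, the covariates are all four baseline near-transfer scores plus the age stratification factor.
- A missing extra baseline score is filled in by a rule that uses baseline data only and ignores condition, so that no child leaves the intention-to-treat analysis because of it.
- The published single-baseline model is reported as a sensitivity analysis.

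If unblinded results have already been seen, the published model should stay primary and the four-baseline model should be labelled supplementary.

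The cost is one line of model specification, a short rule for missing covariates and three degrees of freedom. No new data are needed.
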